## Abstract

**Background:**

Early initiation of alcohol and cannabis use markedly increases the risk of harms associated with use, including the development of substance use and mental health disorders. To interrupt this trajectory, effective prevention during the adolescent period is critical. Despite evidence showing that parents can play a critical role in delaying substance use initiation, the majority of prevention programs focus on adolescents only. Accordingly, the *Climate Schools Plus* (CSP) program was developed to address this gap.

**Objective:**

This paper outlines the protocol for a cluster randomized controlled trial (RCT) of the CSP program, a novel internet-based program for parents and students to prevent adolescent substance use and related harms. The CSP program builds on the success of the *Climate Schools* student programs, with the addition of a newly developed parenting component, which allows parents to access the internet-based content to equip them with knowledge and skills to help prevent substance use in their adolescents.

**Methods:**

A cluster RCT is being conducted with year 8 students (aged 12-14 years) and their parents from 12 Australian secondary schools between 2018 and 2020. Using blocked randomization, schools are assigned to one of the two groups to receive either the CSP program (intervention) or health education as usual (control). The primary outcomes of the trial will be any student alcohol use (≥1 standard alcoholic drink/s) and any student drinking to excess (≥5 standard alcoholic drinks). Secondary outcomes will include alcohol- and cannabis-related knowledge, alcohol use-related harms, frequency of alcohol consumption, frequency of drinking to excess, student cannabis use, parents’ self-efficacy to stop their children using alcohol, parental supply of alcohol, and parent-adolescent communication. All students and their parents will complete assessments on three occasions—baseline and 12 and 24 months postbaseline. In addition, students and parents in the intervention group will be asked to complete program evaluations on two occasions—immediately following the year 8 program and immediately following the year 9 program.

**Results:**

Analyses will be conducted using multilevel, mixed-effects models within an intention-to-treat framework. It is expected that students in the intervention group will have less uptake and excessive use of alcohol compared with the students in the control group.

**Conclusions:**

This study will provide the first evaluation of a combined internet-based program for students and their parents to prevent alcohol and cannabis use.

**Trial Registration:**

Australian New Zealand Clinical Trials Registry ACTRN12618000153213; https://www.anzctr.org.au/Trial/Registration/TrialReview.aspx?id=374178 (Archived by WebCite at http://www.webcitation.org/71E0prqfQ)

**Registered Report Identifier:**

RR1-10.2196/10849

## Introduction

Alcohol and cannabis are the most commonly used licit and illicit drugs in Australia and are associated with substantial socioeconomic costs [1-4]. The initiation of substance use begins during adolescence, and early initiation markedly increases the risk of harms from use and subsequently developing substance use disorders [5]. To interrupt this trajectory, effective prevention during the adolescent period is critical. Traditional approaches to substance use prevention have focused on adolescents only; however, recent evidence suggests that expanding student interventions to include parenting components could markedly increase prevention effects [6-8]. This is because parents are key agents of adolescent socialization, especially in the initiation and development of substance use [9-13], and parenting interventions have been identified as critical components of effective substance use prevention programs [6,9,13,14]. Moreover, adolescent substance use is an area of substantial concern for parents, who generally want to be engaged in substance use harm prevention [15]. Parents also report that they actively seek information about parenting and adolescent substance use; however, most parents are not confident in their ability to stop their child from becoming drunk [16].

Despite the importance of including parents in prevention efforts, relatively few substance use prevention programs have involved both students and parents, and the programs developed have faced numerous challenges during their implementation (eg, high attrition rates, lack of engagement, and lack of sustainability [6,17]). Moreover, no substance use prevention programs that adopt an internet-based delivery approach have involved both parents and students, despite the potential for internet-based delivery to overcome some of the challenges encountered in the implementation and sustainability of prevention programs [6,17]. Therefore, the *Climate Schools Plus* (CSP) program was developed to address this gap and meet the need for a sustainable, evidenced-based student and parent prevention program. Building on the effective internet-based *Climate Schools* drug prevention programs for students [18-21], the CSP program combines the effective *Climate Schools: Alcohol and Cannabis* course for students aged 12-14 years [21-24] with a newly developed parent component [16]*.*

The course is an internet-based universal prevention program delivered to all students regardless of their level of risk and is based on a social influence approach to prevention [22]. The social influence approach has been found to be the most effective approach for school-based prevention programs in decreasing alcohol and cannabis use [22,25]; this approach involves delivering accurate information about substance use, placing substance use within a normative context (ie, most students their age are not using alcohol or cannabis), and developing students’ resistance skills (ie, their ability to identify sources of pressure to use substances and their ability to resist these pressures). The course covers these three components, using cartoon storylines to engage students and is delivered online to ensure high-implementation fidelity. The course consists of 12 internet-based lessons, which align with stage 5 of the Australian Health and Physical Education curriculum; it is designed to be implemented in early adolescence when youth are aged 12-14 years, before marked exposure to alcohol and cannabis occurs. The program has been trialed in two independent cluster randomized controlled trials (RCTs), which have demonstrated the effectiveness of the program in improving alcohol- and cannabis-related knowledge, reducing the uptake and harmful use of alcohol and the frequency of cannabis use up to 2 years following the intervention [18-21]. In addition, the program has been found to reduce psychological distress, moral disengagement (ie, the tendency to disengage from moral self-control and responsibility that ordinarily governs behavior, which has been associated with a range of antisocial behaviors, including heavy drug use and alcohol consumption in young people [26-30]), and truancy [22]. In light of recent evidence, which suggests that expanding universal interventions to include parenting components could markedly increase prevention effects [6], we developed the CSP program [16].

The parent component for the CSP program is based on the successful Dutch Prevention of Alcohol Use in Students (PAS) program [31-33] and was adapted for Australia in consultation with Australian parents and education and health experts [16]. The parent component of the CSP program is designed to be delivered entirely online, across the same school terms as the student *Climate Schools* program. The parent component targets modifiable parenting factors associated with adolescents’ alcohol and cannabis initiation and misuse [10,34], including rule-setting, parental supply, modeling, and monitoring. The parent component comprises introductory webinars, a rule-ranking component, internet-based modules, and internet-based parent summaries of the material covered in the student program. A complete description of the parent component can be found in a development paper published by the members of the research team [16].

Currently, we are seeking to evaluate the effectiveness of the CSP program in preventing alcohol and cannabis use and increasing parents’ self-efficacy to prevent their child from using these substances. Incorporating an internet-based parent component into an effective school-based student program has the potential to remarkably enhance prevention outcomes and reduce alcohol- and cannabis-related harms among adolescents.

We will determine the effectiveness of the CSP intervention by running a cluster RCT in Australian Independent and Catholic secondary schools (ACTRN12618000153213). Cluster randomization will be used to avoid contamination of the control group with the intervention groups through student and staff communication. Schools will be randomly allocated to the CSP condition or the “control” condition. Students and parents in the CSP condition will be provided access to the *Climate Schools*: *Student* component and the *Climate Schools Parenting Program*, respectively, whereas students in the control condition will receive their health education classes as usual, which covers alcohol and other drug education topics. Students and parents in both groups will complete self-report surveys at baseline and 12 and 24 months postbaseline. Figure 1 depicts the study design.

**Figure 1 figure1:**
[figure not shown]
The *Climate Schools Plus* (CSP) intervention trial flow based on the Consolidated Standards of Reporting Trials (CONSORT) guidelines.

## Methods

### Participants, Interventions, and Outcomes

#### Participants

##### Study Setting and Recruitment

This study is set in Independent and Catholic secondary schools in Australia. We obtained Human Research Ethics Committee (HREC) approval to approach Independent schools (HREC 17852) and Catholic schools in two dioceses in the Greater Sydney area (reference: 201731 and 060318) and invite them to participate. In October 2017, 156 schools were approached using a variety of methods, including advertisement during the Personal Development Health and Physical Education (PDHPE) Teachers’ Association Annual Conference, emails sent directly to schools or school principals, newsletter entries (ie, the Independent Secondary Schools Association and *Climate Schools* newsletters), posts on social media, and through follow-up phone calls. Parents will first be recruited to participate in the CSP study when their students bring home the parent permission form, along with a postcard containing information about the study and instructions on how to register. Then, they will also be recruited through an email sent from their school with information about the study, a link to a short, 45-second video introducing the aims of the study and instructions on how to register; this involves parents consenting for their adolescent’s and their own participation. Next, to access the content of the program, parents will need to register for an account through the CSP website. Students who have received parental permission to participate in the study will be approached to register and consent during their regular PDHPE classes and will be given the opportunity to send an email to their parents, reminding them to register for the program through an “Invite Your Parent” icon on the CSP website.

##### Sample Size

For cluster randomization, sample size calculations were based on sample size requirements developed by Heo and Leon [35] to detect the intervention by time interactions in longitudinal cluster randomized clinical trials. This trial is powered to detect differences in the overall student sample across three time-points. Five schools, with an average of 70 students per school, are required per intervention group; this would achieve an 80% power to detect a standardized, between-group mean difference of 0.2 (*P*=.05) in primary outcomes at the end of the trial, with 3 measurement occasions. An effect size of 0.2 is comparable with previous trials of combined student and parent programs (effect size range: 0.2-0.3) [36]. To account for school dropouts during the trial, which we expect to be approximately 15%, we aim to recruit at least 12 schools in total. Assuming that the majority (if not all) students in the year group participate in this study (approximately 70 on average; based on participation rates found in previous school-based trials of a similar nature [18-21,23,24,37]), it will give us a total of 700 students from 10 schools at the baseline to test the effect of the intervention.

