##### Primary Outcomes

###### Any Alcohol Use

Any alcohol use is defined as the consumption of at least 1 full serve or standard drink of alcohol (ie, any drink containing 10 grams of alcohol). To measure this outcome, students would be provided with a chart used to illustrate a standard drink (as used in the NHMRC Australian Guidelines [39]) and asked *“Have you ever had at least one standard alcoholic drink?”* and *“Have you had at least one standard alcoholic drink in the past 12 months?”* Responses to both questions are in the form of “Yes” versus “No.”

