An additional limitation of this study involves the need to obtain active consent from participants, as this might introduce selection bias. We aim to overcome this risk of selection bias with a robust study design. As this is an RCT, both participants in the intervention condition and control condition will volunteer to participate; therefore, the impact of volunteering is likely to be spread evenly across the two conditions. Although active or voluntary consent procedures can introduce selection bias [61], previous studies have found no differences in alcohol or illicit drug use among students with passive or active consent [62]. Moreover, we aim to minimize the chance of selection bias by offering support for participants, to ensure their understanding of the consent form and what is required if they participate in the study (ie, consent forms will be offered in both electronic and hard-copy forms, and if required, the form can be translated into the preferred language of the participants). Ideally, passive consent procedures would be used to maximize the number of participants taking part in the trial; however, ethical restrictions meant that we were required to use active consent procedures in this study. As such, future research would benefit from the use of passive consent procedures to reduce the impact of selection bias on the outcomes in the study.

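### The stated 80% power is for a standardized mean difference, but both primary outcomes are yes/no and analysed by logistic regression, so it is not the power for the primary outcomes; student loss is also left out

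*Protocol article*

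**What the plan says.** All references are to the protocol article.

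- **Sample Size.** The calculation uses a published method "to detect the intervention by time interactions in longitudinal cluster randomized clinical trials". "Five schools, with an average of 70 students per school, are required per intervention group", and "this would achieve an 80% power to detect a standardized, between-group mean difference of 0.2" in the primary outcomes at the trial's end, with alpha 0.05 and three occasions. The value 0.2 is justified as comparable with earlier combined student and parent programs (0.2 to 0.3). School dropout of about 15% raises the target from 10 to 12 schools. Nearly full participation of the year group is assumed from earlier trials, and "it will give us a total of 700 students from 10 schools at the baseline to test the effect of the intervention".
- **Primary Outcomes.** "Any alcohol use is defined as the consumption of at least 1 full serve or standard drink of alcohol", and it is asked as Yes/No. Drinking to excess is also asked as Yes/No. The Outcomes section sets the primary endpoint at 24 months.
- **Statistical Analysis.** Binary outcomes go to mixed-effects logistic regression. The effects of main interest are intervention-by-time interactions. Students have random intercepts and slopes; schools have random intercepts only, although alternative random-effects structures may be compared.
- **Strengths and Limitations.** Student attrition is named as a limitation, without a rate. On recruitment, "ethical restrictions meant that we were required to use active consent procedures in this study".

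**The concern.** The power statement names the primary outcomes but gives the effect on a scale that neither has. A standardized mean difference is not what a logistic model estimates. Without a control rate, odds ratio or risk difference, 0.2 does not fix a detectable effect for either outcome. For binary outcomes, power depends strongly on prevalence, and the two primary outcomes need not have the same prevalence.

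The loss allowance raises a second problem. Only whole schools are inflated for, and the 700 is a baseline count, while the effect is claimed at the end of the trial, two years later.

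At stake is how the result will be read. A null finding would be judged against an 80% figure that was not derived for these outcomes.

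**Working it through.** **Inputs from the Sample Size section:** standardized difference 0.2, alpha 0.05 (two-sided assumed; the article does not say), 5 × 70 = 350 students per arm, 3 occasions, school dropout 15%. **Assumed, because the article gives none:** within-student correlation ρ, between-school ICC, control prevalence, student loss.

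**1. School inflation.** 10/(1 − 0.15) = 11.8, so 12 schools. This reproduces.

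**2. The stated 80%, by a test of the type named.** Take occasions at 0, 1 and 2, a continuous outcome with unit variance, and random intercepts only. School and student intercepts cancel from the slope. The slope difference is 0.2/2 = 0.1, with SE = √((1 − ρ)/n) for n per arm.
- Power = Φ(0.1/SE − 1.96). At n = 350 it is 75.4% for ρ = 0.5, 80.0% for ρ = 0.554 and 84.1% for ρ = 0.6.
- Check at ρ = 0.554: SE = √(0.446/350) = 0.0357; 0.1/0.0357 = 2.80; Φ(0.84) = 0.80.

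The figure is therefore attainable for a continuous outcome.

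**3. What that 80% depends on** (ρ held at 0.554).
- Small-cluster inference: noncentral t on 10 − 2 = 8 df, noncentrality 2.80, gives 69%.
- Schools differing in change: multiply the variance by 1 + 69 × ICC. At an ICC of change of 0.01, 0.02 and 0.05, power is 58%, 44% and 26% (normal), or 47%, 36% and 22% (t on 8 df).
- Student loss, counting lost students as contributing nothing:

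| Students analysed | n per arm | Power |
|---|---|---|
| 100% | 350 | 80% |
| 90% | 315 | 76% |
| 80% | 280 | 71% |
| 70% | 245 | 65% |

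**4. The binary outcomes at 24 months, 350 per arm.** Logit translation of 0.2: OR = exp(−0.2π/√3) = 0.70 (inverse 1.44). Two-proportion normal power with p̄ the mean of p₁ and p₂: Φ{[|p₁ − p₂| − 1.96√(2p̄(1 − p̄)/n)] / √[(p₁(1 − p₁) + p₂(1 − p₂))/n]}. For the last column, n = 350/(1 + 69 × 0.02) = 147.

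| Control rate | Intervention rate | Power, no clustering | n per arm for 80% | Power, ICC 0.02 |
|---|---|---|---|---|
| 10% | 7.2% | 27% | 1544 | 14% |
| 20% | 14.8% | 44% | 839 | 22% |
| 30% | 23.0% | 56% | 618 | 28% |
| 40% | 31.7% | 63% | 522 | 32% |
| 50% | 41.0% | 67% | 483 | 34% |

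**5. The more favourable translation.** Read as Cohen's h, 0.2 means 20% falling to 12.7%, or 10% falling to 4.8%. Unclustered power at 350 per arm is then 75% and 74%. That is close to the 75.4% for a continuous single-time comparison: Φ(0.2√175 − 1.96) = 0.754.

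**The case against.** The best defence is that the article names a longitudinal interaction method, and a test of that type returns 80% at an ordinary within-student correlation. This stands. A reader might infer that the 80% cannot be obtained at all. The documents do not support that; the figure cannot be checked from the stated inputs, which is a weaker statement.

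A reader might also argue that 350 per arm leaves no room for school clustering, because a two-group comparison of 0.2 needs 2(1.96 + 0.8416)²/0.04 = 392.4, so 393 per arm, even without clustering. That is the benchmark for a single time point. The planned contrast is group by time, and in a linear model a school random intercept cancels from it, which matches the school-level structure in the Statistical Analysis section. What remains is that between-school variation in change is taken as zero, and that the cancellation is exact only for linear models, not for the logistic models planned for the primary outcomes.

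Nor is non-consent ignored. The Sample Size section states a participation assumption and cites earlier trials for it. Beside required active consent it may be optimistic, but those trials' participation rates and consent procedures cannot be seen here.

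On student loss, maximum likelihood keeps partly observed students, so counting them as contributing nothing overstates the drop for a given loss rate. Finally, an article may leave an ICC or correlation to a fuller document, and their absence alone is not the point. The point is that a specific power is claimed for specific outcomes on a scale that does not fit them.

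**Conclusion.** The point holds in a limited form. The 80% is a power for a continuous outcome and should not stand as the power for two binary primary outcomes. Even on its own scale it requires ρ of about 0.55, no between-school variation in change, normal rather than small-cluster inference (69% with t on 8 df) and complete student follow-up (71% with 20% loss).

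The size of the shortfall for the binary outcomes is not fixed by the documents. Without clustering it runs from 27% to 67% power at OR 0.70 for control rates of 10% to 50%, and is about 75% if 0.2 is read as Cohen's h. These are single-time comparisons that use neither baseline nor repeated measures, and the prevalences, ICCs and loss rates are assumptions. A reader might conclude that the trial could detect only large effects; the documents do not establish that. They establish that the stated figure was not derived for the outcomes it is attached to, and that the only loss inflated for is at school level.

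**What to change.** In the Sample Size section, restate the power for each binary primary outcome at 24 months with the planned 10 to 12 schools. Alternatively, give the risk difference or odds ratio detectable with 80% power. State the inputs:

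- control prevalence for each outcome;
- between-school variation, including variation in change;
- within-student correlation;
- students analysed per school after attrition;
- inference suited to a small number of clusters.

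Give a short range where an input is uncertain. Stop presenting 80% for a standardized difference of 0.2 as the power for the primary outcomes. If it is kept, label it as applying to a continuous outcome and give the correlation used.

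The cost is a recalculation and probably a less favourable stated figure. The design and recruitment target do not change.

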##### Eligibility Criteria

Eligible participants are students attending participating schools and are enrolled in year 8 in 2018 and these students’ parents. These students will be 12-14 years of age at baseline and 14-16 years of age at the final assessment point. Furthermore, to be eligible to participate, students and parents must have at least intermittent internet access and basic proficiency in English.

##### Consent or Assent

After school principals agree to participate in the study, active consent will be sought individually from parents, students, and teachers. Parents will be asked to provide active consent for (1) their child’s participation in the study and (2) their own participation. Eligible students with parental consent will be directed to the participant information statement and consent form when registering on the CSP website, and all parents will similarly be directed to their participant information statements and consent forms when registering for the first time. Conversely, students and parents in the CSP group who do not consent to participate in the research trial will still be offered access to the content of the program; however, they will not be prompted to complete assessment surveys, and no data will be collected from those individuals.

